### Objective and aims

The overarching aim of this study is to elucidate potential pathways of stress and stress-related concepts with subsequent health behaviors during a behavioral weight loss intervention. The primary exposure is the difference (i.e., variability) in signal-contingent survey stress, coping, and affect early in the program. The primary outcome is weight change across a behavioral weight loss program, and secondary outcomes are physical activity and sleep. We hypothesize that high variability in daily stress will be related to less weight loss across the initial (12-weeks) and full (26-weeks) program (Hypothesis 1a). Our second hypothesis is that high variability in daily stress will be related to less physical activity and sleep across the initial and full program (Hypothesis 1b). These hypotheses were constructed as higher variability and fluctuations aligns with past literature that with individuals who experience lower stressful daily events and who are able to cope consistently and easily with this daily stress may be more active and lose more weight compared to individuals experience daily changes in stress and are less able to cope or find it difficult to do so [5,14]. Finally, we hypothesize that high variability in coping and positive affect will be related to less weight lost across the initial and full program (Hypothesis 2).

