#### Ecological momentary assessment (EMA).

Participant’s current state and behaviors will be collected using a customizable software (LifePak, LifeData Corporation, Marion, IN). This software is compatible with both Apple and Android iOS delivered phone notifications as reminders, and study surveys will be completed within the app. Questions occur in the same order for all surveys and are provided as supplementary material (S2–S4 Tables) and a detailed account of constructs is provided in Fig 1. Participants will receive six surveys, including four signal-contingent and two fixed surveys (i.e., available for a fixed time period), through the app each day for 14 continuous days as performed by others measuring physical activity [20]. Signal-contingent surveys occurred randomly within fixed 3-hour windows (8:00am–11:00am, 11:00am-2:00 pm, 2:00 pm-5:00 pm, and 5:00–8:00 pm) and expire 45 minutes after the initial reminder. The two fixed surveys include the morning and evening survey; the morning survey will be available for four hours (8:00am-12:00 pm), and three hours for the evening survey (5:00–8:00 pm). These schedules may be shifted for non-traditional schedules, such as shift work, to ensure participants are available to answer these questions during their waking hours. Participants will be provided with three reminders for signal-contingent surveys, including the initial reminder, and reminders at 15-minutes and 30-minutes, if necessary. Participants will be sent reminders for the morning and evening surveys every hour, if necessary. Sampling time frames and prompt strategies were informed by past EMA studies [21,22]. Participants will be expected to complete at least one morning survey and two within-day surveys (~50%) for 5-days [23], with an additional incentive for 7-days in a row as conducted in our preliminary EMA studies.

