#### Other stress-related states, and health behaviors.

As shown in Table 1, morning, signal-contingent, and evening surveys will assess other relevant considerations. The morning survey includes 16 questions, ending with the two questions that assess stress and coping. Participants will be asked, based on the previous night, how many hours of actual sleep they received, their bedtime and wake-time, and overall sleep quality. These questions are adapted from the Pittsburgh Sleep Quality Index, which is validated in adults [27]. This is followed by two questions on accelerometer and saliva compliance and then questions related to coping with stress and cravings the previous day. Cravings will be assessed using an adapted momentary scale of the Food Cravings Inventory (FCI). The FCI is questionnaire queries five different subscales including high fat foods, sweets, carbohydrates/starches, fast foods, and fruits and vegetables; this scale has been validated in adults [28]. FCI responses are via a 5-point scale, with higher scores indicating more frequent cravings. In the momentary question, we will ask how often they felt cravings for each of the 5-main items, with similar Likert scale responses. For example, they will be asked how frequent they craved carbohydrates/starches during the day. They will be asked if they indulged in cravings, and if so, which of the five craving groups with check box option.

**Table 1 pone.0357572.t001:** Daily Schedule of Ecological Momentary Assessment Surveys sent to participants for 14-days.

Construct	Morning Survey (8a-12p)	Period 1 (8a -11a)	Period 2 (11a -2p)	Period 3 (2p-5p)	Period 4 (5p-8p)	Evening Survey (6p-10p)
Sampling	Fixed	Random	Random	Random	Random	Fixed
*Stress and stress-related concepts*						
Acute Stress	x	x	x	x	x	x
Coping Mechanisms	x					x
Affect		x	x	x	x	
Chaos/ Disorder		x	x	x	x	x
Context		x	x	x	x	
*Health Behaviors*						
Diet	x					x
Cravings	x					x
Physical Activity						x
Sleep	x					
Survey Burden						x

Participants will also be surveyed about accelerometer wear at night and salivary cortisol collection in the morning survey, and accelerometer wear during the day will be queried in the evening survey.

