### Analytical approach

#### Aim 1: Examine the association between variability in individual stress and weight change.

For hypothesis 1a, that high variability in daily stress will be related to less weight loss, linear regression will examine week-0 average and change frequency in daily stress (morning survey) with weight change at week-12 (visit 3) and week-26 (visit 4). For hypothesis 1b, that high variability in daily stress will be related to less physical activity and sleep, multi-level models with logit link function (and binomial distribution) will be used to examine association between week-0 morning stress and same day MVPA and sleep, with an interaction of time/day*morning stress. For exploratory analyses, we will examine the associations of daily stress with MVPA and sleep at other time points (week-6, week-12, and week-26), lagged day effects of stress (i.e., stress on day 1 influencing MVPA and sleep on day 2) to preserve temporal ordering and considering inverse probability weighted marginal structural models, and the outcome of weight change at week-6.

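### The model planned for Hypothesis 1b uses the daily level of morning stress at week 0, so it cannot test stress variability or the 12- and 26-week horizon that the hypothesis names

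*Protocol article*

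**What the plan says.** All references are to the Protocol article.

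- **Hypothesis** (Objective and aims): "high variability in daily stress will be related to less physical activity and sleep across the initial and full program". The same section defines the initial program as 12 weeks and the full program as 26 weeks.
- **Exposure** (same section): "The primary exposure is the difference (i.e., variability) in signal-contingent survey stress, coping, and affect early in the program".
- **Model for Hypothesis 1b** (Analytical approach, Aim 1): "multi-level models with logit link function (and binomial distribution) will be used" to examine the "association between week-0 morning stress and same day MVPA and sleep, with an interaction of time/day*morning stress".
- **Later waves** (same section): "For exploratory analyses, we will examine the associations of daily stress with MVPA and sleep at other time points", namely weeks 6, 12 and 26. A lagged-day analysis, meant to keep stress ahead of the outcome, is also exploratory.
- **Neighbouring models** (Aims 1 and 2): Hypotheses 1a and 2 regress weight change at weeks 12 and 26 on the week-0 average and change frequency of stress, or of coping and positive affect.
- **Morning survey**: "Participants will be asked, based on the previous night, how many hours of actual sleep they received" (Other stress-related states, and health behaviors). The current-stress rating, 0 to 10, comes at the end of that survey.

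**The concern.** The hypothesis compares people by how much their stress fluctuates and looks ahead to weeks 12 and 26. The model compares days by how high stress was that morning and stays in week 0. These are different exposures over different periods, and either can show an association without the other.

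A null result from the planned model could therefore be reported as evidence against Hypothesis 1b, or a significant one as support, when variability was never estimated. The sample-size section also argues for 50 participants by expecting to detect stress variability against physical activity and sleep, which is the association this model leaves out.

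A smaller point concerns the same-day model itself. It does not say which night is same-day sleep. If it is the night reported in the morning survey, the outcome comes before the stress rating.

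**Working it through.** **1. Hypothesis and model side by side**

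| Element | Hypothesis 1b | Planned model |
|---|---|---|
| Exposure | Variability in daily stress (one value per person) | Morning stress level (one value per day) |
| Outcome period | To week 12 and to week 26 | Same day, week 0 |
| Waves used | Through the program | 1 of 4 |

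**2. What the model's coefficients measure.** For person *i* on day *j*, with stress S and centred day t, the text implies

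logit P(Y_ij = 1) = b0 + b1·S_ij + b2·t_j + b3·S_ij·t_j + u_i.

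Here b1 is the slope of the day's outcome on that day's stress level, and b3 is the drift of that slope over days. Averaged over a person's days, the linear predictor is b0 + b1·mean(S_i) + b3·mean(S_i·t) + u_i. It depends on the person's mean stress and its linear trend, not on the spread V_i. Hypothesis 1b needs a coefficient on V_i, and there is none. Splitting S_ij into person mean and daily deviation would not supply one. Nor would another link function, since the link acts on the outcome side.

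**3. Whether the exploratory analyses fill the gap.** They repeat the daily-stress association at later waves. None relates week-0 variability to week-12 or week-26 outcomes.

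**4. Illustration by simulation** (assumed effects; the conclusion does not rest on it). Setup: 50 people, 14 days, binary daily outcome, 400 runs, tests at 0.05. Person means were normal (mean 4, SD 1.5), within-person SD uniform from 0.5 to 3, and the random intercept SD 0.5. A population-averaged logit model stood in for the multi-level one. The comparator was a person-level regression on within-person SD plus mean stress.

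| Truth assumed | Level term rejects | Level × day rejects | Within-person SD term rejects |
|---|---|---|---|
| Variability only (log-odds −0.6 per point of SD) | 6.25% | 5.75% | 90.75% |
| Level only (log-odds −0.2 per point) | 100% | 7% | 5.5% |
| Neither | 7.5% | 4.25% | 7.75% |

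The Monte Carlo standard error at 5% is √(0.05 × 0.95 / 400) = 1.1 points, so the tests run slightly liberal. The contrast is clear all the same. With a variability effect only, the planned terms reject at about their null rate; with a level effect only, the planned term always rejects although Hypothesis 1b is false. The 90.75% reflects the assumed effect and is not the power of this study. The simulation covers the exposure mismatch, not the horizon.

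**5. The plan's own figure.** The sample-size section gives 0.80 power at n = 50 for a random linear regression (effect size 0.3, alpha 0.01, five predictors, critical R² 0.27). Reading 0.3 as the squared multiple correlation, power at n = 50 is 0.773, and 0.80 needs 53. Critical R² = kF/(kF + N − k − 1) is 0.283 at N = 50 and 0.268 at N = 53. That is close but not an exact match. It concerns a person-level linear regression, not the daily logit model, and nothing here depends on it.

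**The case against.** **A condensed article may omit terms.** True in general, but the adjacent sentence for Hypothesis 1a and the paragraph for Hypothesis 2 both name change frequency. For Hypothesis 1b the text states a different exposure outright.

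**Time in the interaction might mean visit.** Even so, the exposure is week-0 morning stress and the outcome is same-day, which keeps the outcome in week 0.

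**These are secondary outcomes.** This stands. The weight-change models for Hypotheses 1a and 2 carry average and change-frequency terms at weeks 12 and 26, so a reader should not infer that the primary analysis is compromised.

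**Temporal order is partly handled.** Also fair. The protocol plans lagged effects, considers marginal structural models, and words Hypothesis 1b as an association. Three stronger readings are tempting, but the documents do not support them:

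- *Every sleep outcome precedes its exposure.* The text does not say which night is meant, and the secondary sleep outcome draws on overnight accelerometry as well as questionnaires. This is an ambiguity, not a demonstrated reversal.
- *A quarter of the day's MVPA precedes the rating.* The survey section says "the morning survey will be available for four hours (8:00am-12:00 pm", and 4 h over an assumed 16 waking hours is 25%. But the 16 hours are not in the document, activity before 8:00 would add to the 4, schedules may be shifted, and no response times are given. The figure is neither an estimate nor an upper bound.
- *Stress enters uncentred, mixing between- and within-person effects.* The article does not say so, and centring is commonly left to the analysis plan.

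**Conclusion.** The mismatch is in the text and needs no outside assumption. The planned analysis of Hypothesis 1b has no variability term, uses one of four waves, and has no week-12 or week-26 outcome. As written it can neither support nor refute the hypothesis. The reach is one named hypothesis on the secondary outcomes, plus the sample-size rationale that cites the same association. It does not follow that the study cannot address Hypothesis 1b: the planned measurements allow it, and only the stated model does not. Which night counts as same-day sleep is a secondary gap in definition.

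**What to change.** 1. **Test the stated hypothesis.** Model MVPA and sleep at week 12 and week 26, for example in a mixed model across visits, on week-0 person-level stress variability (the change-frequency measure of Hypothesis 1a) and week-0 mean stress. Include variability × visit and report the variability effect at each of the two visits. Keep the same-day level model as a separate, clearly labelled analysis.
2. **Or restate the hypothesis** as one about same-day stress level at week 0, and align the sample-size rationale with it.
3. **In the same-day model**, define same-day sleep and pair morning stress with the following night. Truncating MVPA at the survey response is not advised: the article does not mention survey time stamps, and late responders would have shorter outcome windows.

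**Cost.** Wording and code only. Week-0 morning stress and 14 days of accelerometry after each of the four visits are already planned. Nine participants were enrolled as of January 2026, so the change can precede analysis.

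**Downside.** The variability term rests on 50 people, against 5 × 50 = 250 daily observations at minimum compliance and 14 × 50 = 700 at full compliance. If variability were a within-person SD of roughly normal, independent ratings, its relative standard error per person would be about 1/√(2(n − 1)): 1/√8 = 35% with 5 days and 1/√26 = 20% with 14. Precision will be lower than for the daily-level term, but the estimate will answer the stated question.

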#### Aim 2: Examine the association between variability in coping and positive affect and weight change.

To address hypothesis 2, that high variability in coping and positive affect will be related to less weight loss, linear regression will examine week-0 average and change frequency in coping (morning survey) and positive affect (within day survey) with weight change at week-12 and week-26.

Potential covariates for both models include number of ACEs, program compliance (i.e., number of sessions attended), coping mechanisms (number and type), age, and sex. Statistical significance will be set at *p* = 0.05. All available data will be analyzed with a sensitivity analysis for individuals with complete data. Significant weight loss will be seen at 12-weeks (12.7 ± 19.9 kg), and 6-months (12.7 ± 35.2 kg) based on past studies in our community-based weight loss program allowing us to compare weight loss in Hypothesis 1a and 2. [15]

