### Participants, eligibility, and recruitment

This study seeks 50 individuals who are newly enrolled in a community-based weight loss program centered in a metropolitan area of a Midwest state. Participants will be recruited from an existing 6-month-long community-based weight management program hosted by the University of Kansas Medical Center, local Diabetes Prevention Programs and other behavioral weight loss programs in the local area that may range from 6 to 12-months long. These weight management programs typically include trained health educators, 1-hour weekly video meetings, group peer support, structured nutrition plan (low calorie diet), personalized activity recommendations, and behavior change modifications [15]. Prospective participants will be recruited at their initial consultation or orientation visit for their behavioral weight loss program. Flyers will also be presented to participants at their initial visit. Measures were planned to coincide with initial enrollment (week-0), early weight change (week-6), and later weight change measures (week-12, week-26).

To be included, participants must be newly enrolled or plan to enroll in a community-based weight management program, must be over 18 years of age, have body mass index (BMI) ≥30 m/kg^2^, own a smartphone and be willing to download the mobile application to receive text messages [16]. Participants who chose to cease their community-based weight management program involvement after enrolling in the INSTANT study can still participate in later assessments, improving upon past studies which only included individuals who completed their program [17,18]. Indeed, stress may impact continued engagement in a weight management program. Participants will be excluded for being currently prescribed FDA-approved medications for weight loss, treatment for a medical condition that could affect body weight, or impacting stress levels (e.g., antidepressants), a current psychological condition that is untreated, hospitalization for a psychological condition within the past 12-months, or not being on a stable dose of treatment for at least 6-months. Other exclusion criteria are not being fluent in writing or speaking the English language, mobility limitations so they are unable to perform physical activity, and a family member who was previously enrolled or is currently enrolled in the study.

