#### Exploratory outcomes.

Stress will be assessed at the individual level (chronic, current, and early life exposure) and at the home level (current household chaos). Chronic stress will be assessed as both stressful life events, and overall stress in the past month. First, the Brief Life Event Questionnaire will be used to assess chronic stress each 3-months (Visit 1, Visit 3, Visit 4). This questionnaire is a self-report measure to quantify presence of potentially traumatic and stressful events (e.g., close family member died, major financial crisis), and whether they still think about the event a lot, a little, or not at all [23,30]. Specifically, participants will be surveyed about the presence of each event within the last 6-months, or since they completed the questionnaire. This questionnaire has demonstrated high test-retest reliability (kappa: 0.88–1.0), and high sensitivity and specificity for the previous 6-months (0.89, 0.74, respectively) [39]. Second, recent stress in the past month will be assessed using the 10-item Perceived Stress Scale. This is a scale a questionnaire about feelings and thoughts over the last month, and has demonstrated in adults high values in metrics of validity and reliability [40]. Third, the early life exposure to stressful events, especially during critical periods of growth, may impact child development and later health [41,42]. We will assess adverse child experiences (ACEs) through 11 questions which query participants about events that happened prior to age 18 years old. These queries will be about family dysfunction (e.g., family member with mental illness, member in prison), and abuse (physical, verbal, etc.), and are adapted from the Behavioral Risk Factor Surveillance System ACE module, which is conducted nationwide in adults [43]. This scale’s validity and reliability was recently examined using measurement invariance, and demonstrated the total scoring is appropriate for analysis [44]. Total number of ACEs will be a potential mediator in analysis. Finally, the Confusion, Hubbub, and Order Scale (CHAOS) is a 15-item measure assessing disturbance, organization, and noise levels in the home. It has been validated in parents of young children to assess the home environment [29], and will be assessed at each visit.

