#### Demographics and program attendance.

Participants will report demographic characteristics (e.g., age, race/ethnicity, income) and previous weight loss history at baseline. Enrollment in the program will be queried from the respective programs at initial screening to confirm meeting inclusion criteria. Final session attendance dates will be queried from the program at end of study.

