#### Data management plan.

All participants will be given an ID as part of the screening process. This ID will be stored on a secure database at the University of Kansas Medical Center. Only approved project staff will have access of the server. At each major time point (week-0, 6-weeks, 12-weeks, and week-26), we will collect other participant data including anthropometry (weight and height), accelerometry, questionnaires related to participant behaviors, stress, and stress-related states. Program attendance data will be collected after Visit 4. These values will be reported as tabular data and stored in a secure electronic data capture system. All subject-level clinical data will be preserved and shared. Shared data will be deidentified, and the original data will be maintained at the investigator’s institution. Completed salivary tubes will be frozen until analysis and stored at a biospecimen freezer at the local site. This data will be processed within 1-year of collection to calculate salivary cortisol, and remaining biospecimen will not be stored.

Missing data and data quality will be assessed throughout the study, including REDCap validation rules, double data entry of values (e.g., height and weight), reviewing participant salivary collection logs, and periodic review of study records. For EMA, participants are contacted multiple times during their use period to ensure compliance and any technical issues that may impact obtaining data. For accelerometry, device non-wear periods and implausible values will be identified through reviewing device wear logs and routine quality control procedures of devices. During analysis, we will examine patterns of missing data. If appropriate, mixed models will be used; these models are robust to incomplete repeated measures under a missing-at-random assumption. Further, sensitivity analyses may be considered to evaluate the impact of missing data on study findings.

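### Sessions attended accrues after the week-0 exposure and may depend on stress, yet it is a candidate covariate in the weight models with no counting window

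*Protocol article*

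**What the plan says.** **Exposure and outcome.** For Hypothesis 1a, "linear regression will examine week-0 average and change frequency in daily stress (morning survey) with weight change at week-12" and at week 26 (Analytical approach, Aim 1). Hypothesis 2 uses the same form for coping and positive affect, again measured at week 0 (Aim 2).

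**Covariates.** Aim 2 closes with "Potential covariates for both models include number of ACEs, program compliance (i.e., number of sessions attended), coping mechanisms (number and type), age, and sex". I read this as covering the weight models of both aims. No time point is given for coping mechanisms, which are asked about at visits and also in the daily surveys.

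**Stress and attendance.** Participants who leave their program may stay in the study. The stated reason is: "Indeed, stress may impact continued engagement in a weight management program" (Participants, eligibility, and recruitment).

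**Attendance data.** "Final session attendance dates will be queried from the program at end of study" (Demographics and program attendance), and "Program attendance data will be collected after Visit 4" (Data management plan). Neither section says up to which date sessions are counted. Recruitment includes "other behavioral weight loss programs in the local area that may range from 6 to 12-months long".

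**ACEs.** Exploratory outcomes states: "Total number of ACEs will be a potential mediator in analysis". The same section defines ACEs as events before age 18.

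**The concern.** A covariate that arises after the exposure and may be caused by it is not a confounder. By the protocol's own reasoning, stress at week 0 may reduce attendance, and attendance is part of how a weight loss program works. Holding attendance fixed then changes the question from whether people with more variable stress lose less weight to whether they lose less weight given equal attendance. The hypotheses are worded as the first question.

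Two further problems follow. If something unmeasured, such as motivation, drives both attendance and weight, conditioning on attendance can produce a stress coefficient where no effect exists. And if the count runs to week 26, the week-12 model adjusts for sessions held after its outcome, which early weight loss may itself influence.

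At stake is the meaning of the coefficient for the primary outcome.

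**Working it through.** The protocol has no figure to reproduce here, so the check is the order of events plus an illustration.

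**1. Order of events**

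| Item | When it is fixed | Source |
|---|---|---|
| ACEs | before age 18 | Exploratory outcomes |
| Age, sex | by week 0 | Demographics |
| Stress, coping, affect (exposures) | 14 days from the day after the baseline visit | Baseline; Aims 1 and 2 |
| Sessions attended | accrues through the program | Aim 2; Demographics and program attendance |
| Weight change | week 12 and week 26 | Aims 1 and 2 |
| Attendance data obtained | after Visit 4 (week 26) | Data management plan |

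Attendance follows the exposure for both outcomes. For the week-12 outcome, nothing excludes sessions from week 12 onward.

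**2. Loss through the attendance path.** Let *a* be the effect of stress on attendance, *b* that of attendance on weight loss, and *c* the direct effect of stress on weight loss. All values are assumed, because the documents give none. In a linear model without unmeasured common causes:

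- coefficient without attendance = c + a·b
- coefficient with attendance = c
- share lost = a·b / (c + a·b)

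Power is two-sided at 5% from a simulation with n = 50 and 4,000 replicates; stress, attendance and the weight residual have unit variance.

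| a | b | c | Without attendance | With attendance | Share lost | Power without / with |
|---|---|---|---|---|---|---|
| 0 | 0.4 | −0.3 | −0.30 | −0.30 | 0% | 0.47 / 0.52 |
| −0.2 | 0.4 | −0.3 | −0.38 | −0.30 | 0.08/0.38 = 21% | 0.68 / 0.51 |
| −0.4 | 0.4 | −0.3 | −0.46 | −0.30 | 0.16/0.46 = 35% | 0.83 / 0.45 |
| −0.5 | 0.6 | −0.1 | −0.40 | −0.10 | 0.30/0.40 = 75% | 0.66 / 0.09 |

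If only *a* changes, with c = −0.15 and b = 0.5, the loss is 0.10/0.25 = 40% at a = −0.2 and 0.20/0.35 = 57% at a = −0.4. If the whole association ran through attendance (c = 0), all of it would be lost.

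**3. Spurious association from an unmeasured common cause.** Assume no effect of stress or attendance on weight (b = c = 0), a = −0.4, and a common cause with loading 0.5 on both attendance and weight. Given stress, attendance has variance 1 − 0.16 = 0.84 and covariance 0.25 with weight loss. The stress coefficient becomes 0.4 × 0.25/0.84 = +0.12 instead of 0. In the simulation the rejection rate rises from 4.9% to 10.6%.

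**4. Sessions counted after the week-12 weight.** Assume no stress effect on week-12 loss, and later attendance that depends on that loss (0.4) and on stress (−0.3). With unit residual variance in attendance the stress coefficient is 0.3 × 0.4/1.16 = +0.10. With attendance standardised it is 0.3 × 0.4/0.91 = +0.13. The true value is 0 in both cases.

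**5. ACEs.** Events before age 18 cannot lie between a week-0 exposure in adults and later weight. The mediator label does not fit; the covariate role does.

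**The case against.** The covariates are only called potential. The power section allows up to five predictors, while two exposure terms (average and change frequency) plus ACEs, sessions, coping number, coping type, age and sex make at least 2 + 6 = 8. The list is therefore a set of candidates, and the final choice may stand in an analysis plan that is not shown. This stands: a reader might infer that over-adjustment is certain, and the text does not support that. It does not remove the point, because the protocol names a post-exposure variable as eligible, and leaving it optional allows a choice between two different quantities after the data are seen.

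A reader might also infer that attendance arrives as one end-of-study total. The text speaks of attendance dates, so a count cut off at week 12 may be feasible. The fault is the unstated window. A cut-off would cure the post-outcome problem but not the mediator problem.

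Program length is a weak argument. If the data are drawn soon after Visit 4, counts from 6- and 12-month programs cover about the same calendar period.

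An association given equal attendance is a legitimate quantity in an observational cohort, and the protocol declares neither a total nor a direct effect. That is fair, but Hypotheses 1a and 2 carry no such condition.

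Finally, the two descriptions of ACEs might be read as further over-adjustment. They are not: adjusting for an earlier factor is ordinary, and only the label is wrong.

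**Conclusion.** The point holds as a risk in the stated covariate set. If sessions attended enters the main weight models, the coefficient no longer estimates the association that Hypotheses 1a and 2 describe, and at week 12 it may also be conditioned on events after the outcome. The same question arises for coping mechanisms if they are taken from visits after week 0.

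The size cannot be derived from the documents. The range of 0% to about 75% shrinkage rests wholly on assumed linear paths with part of the effect direct; the lower end applies if stress does not affect attendance. A reader might conclude that the bias always runs toward zero. With shared unmeasured causes or post-outcome sessions it can instead create an association, so its direction is uncertain too. The ACE inconsistency is a minor labelling matter and does not affect the weight coefficient.

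**What to change.** - Limit the main models for Hypotheses 1a and 2 to covariates fixed at or before week 0: age, sex, ACEs, and coping mechanisms from the baseline visit, with that time point stated.
- Use sessions attended only in a separately labelled mediation or direct-effect analysis, counted up to each outcome visit and preferably as a share of sessions offered. Ask the programs for dated attendance so that this is possible.
- In Exploratory outcomes, drop the mediator label for ACEs and give them one role, as a baseline covariate.

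The cost is wording. Nine participants were enrolled as of January 2026 and results are expected in 2027, so the change can precede any result. The downside is slightly more residual variance in the main model: in the assumed case with no link between stress and attendance, power is 0.47 without attendance and 0.52 with it. The reduced list, with two exposure terms, still has to be fitted to the five-predictor limit in the power section.
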